## Background

India is the world’s largest contributor to child malnutrition. Approximately 50% of all children are underweight and about three-fourths are anemic. Maternal undernutrition and anemia are also very common. About 36% of Indian women are classified as underweight and likely to suffer from chronic energy insufficiency according to body mass index (BMI). The prevalence of maternal anemia is about 52%.

Despite decades of continued programmatic efforts, levels of malnutrition in India remain high. The proposed ER, therefore, seeks to:

1. Implement and evaluate the impact of a package of services designed to improve the nutritional status of mothers and children, and
2. Build on the lessons learned through these programmatic efforts.

*INHP-II ‘Basic Package’*

CARE-India's Integrated Nutrition and Health Program supports the efforts of the GOI to improve nutrition status of women and children in India through the Integrated Child Development Services program. The INHP-II “basic” package of interventions is, thus, focused on reducing the prevalence of childhood underweight and anemia within the framework of existing national programs and policies. This basic package is ultimately scheduled for large-scale implementation in 8 additional states as part of INHP-II.

The package (see Table 1 for details) includes prenatal nutrition, early initiation of and sustained exclusive breastfeeding for six months, continuation of breastfeeding with appropriate complementary feeding from 6-24 months (including feeding during and after illness), and iron and vitamin A supplements for children. This is part of a broader package of essential child health and nutrition interventions that also include newborn health and routine immunization.

A specific thrust of INHP-II is to address system constraints to program effectiveness within the public health system. These include inadequate staffing and supervision; interruptions in supplies; lack of coordination amongst programmatic partners; and poor information systems for management. INHP-II’s premise is that strengthening the capacity of service providers and communities will enhance the effectiveness of programs. Enhanced efficiency of service providers is, in turn, expected to promote improved dietary practices during pregnancy, lactation and infancy, timely immunization, optimal breastfeeding and young child feeding practices, and appropriate micronutrient supplementation. The service providers referred to here include Anganwadi Workers (AWWs) and Auxiliary Nurse Midwives (or ANMs). Community capacity is to be strengthened mainly by building capacity of ‘change agents’ and Community Based Organizations (CBOs). It is expected that these key capacity-building interventions will improve maternal and child nutritional status.

This proposal describes the plan for evaluating the impact of this basic package. This will be compared to a control arm in which the Government of India’s (GoI’s) Integrated Child Development Services (ICDS) program is operational.

Although integrated programs are not uncommon, few rigorous evaluations of such programs have been conducted. The ER will therefore make a valuable contribution to current knowledge on program effectiveness.

*Is program customization necessary for different regions in India?*

The economic and cultural heterogeneity of the Indian population raises concerns about whether programmatic efforts should be tailored to different regional settings in order to reduce maternal and child malnutrition. These concerns about program design are bolstered by the fact that previous programmatic efforts in the poorer states in India have not demonstrated improvements in child nutritional status. This is despite evaluations demonstrating the strength of the program implementation and evidence of behavior change. This raises two related questions:

1. Given the scope and density of such programs, are they likely to be more effective in areas where constraints to adequate child growth are less formidable?
2. Alternatively, is this a problem related to evaluation time-frame constraints? In other words, is it that program effectiveness is more easily demonstrated within a limited time frame in areas where constraints to adequate child growth are less formidable?

The proposed ER, therefore, seeks to implement and assess INHP-II activities in 2 Indian states that provide distinct ecological settings─ Uttar Pradesh (UP) and Andhra Pradesh (AP). UP has high rates of child undernutrition and infant mortality. In addition, UP is the location of the Newborn Care Evaluation Research Project that will bring additional supervisory resources and therefore facilitate close supervision of the sites. AP, on the other hand, has better nutritional status compared to all India figures, a receptive state government, high capacity to operationalize and monitor implementation of the ER activities and high potential uptake of ER results.

Table 1. Key components of the Basic Nutrition Package of INHP

| **Life Cycle Period** | **Basic Package** |
| --- | --- |
| Pregnancy | *3 contacts*   - Iron Folic Acid (IFA large) supplementation - Rest for 1-2 hours - Dietary advice - Consume one additional meal everyday - Consume all available foods in the house - Consume Supplementary Nutrition (SN) |
| Birth- 28 days | *3+ contacts at 0, 3 and 7 days*   - Initiate breastfeeding within 1 hour - Exclusive breastfeeding - Make sure baby is getting as much milk as possible, e.g. correct position and attachment - Feed from one breast until soft and then switch to the other in order for child to receive fore and hind milk   For newborn who does not feed vigorously; provide expressed breast milk with clean cup and spoon as long as breastfeeding is not adequately vigorous; frequent feeding   - Dietary advice for mother - Consume one additional meal everyday - Consume all available foods in the house   Consume SN |
| 1-5 months | *3 contacts at 1.5, 2.5 and 3.5 months*   - Exclusive breastfeeding for 6 months - Dietary advice for mother - Consume one additional meal everyday - Consume all available foods in the house - Consume SN |
| 6-8 months | *1+ contact*   - Continued breastfeeding - Appropriate Complementary Feeding - Initiate complementary foods: rice, dal, *suji*, banana etc. - Start with few teaspoons and gradually increase the quantity - Child should be fed 1/2 *katori* of soft mashed food 3 times a day, with 1/2 to 1 tsp of oil added - Feed the child yourself from a separate plate or bowl to assess how much the child has eaten; interact with the child - During illness breastfeed more frequently, provide fluids - After illness give more food at each sitting and feed more frequently until the child has regained weight |
| 9-11 months | *1+ contact*   - Continued breastfeeding - Appropriate Complementary Feeding - Child should be fed 1/ 2 *katori* of soft mashed food (rice, *dal*, vegetables, green leafy vegetables, fruits. Milk products, egg , meat , fish if available and feasible) 4 times with 1 tsp of oil added - Feed the child yourself from a separate plate or bowl to assess how much the child has eaten; interact with the child - During illness breastfeed more frequently, provide fluids - After illness give more food at each sitting and feed more frequently until the child has regained weight   Vitamin A and measles immunization at 9 months |
| 12-24 months | *2+ contacts*   - Continued breastfeeding - Appropriate Complementary Feeding - Child should be fed 3/4 *katori* of soft mashed food (rice, *dal*, green leafy vegetables, other vegetables, fruits. Milk products, egg , meat , fish if available and feasible) 4-5 times a day with 1-2 tsp oil - Feed the child yourself from a separate plate or bowl to assess how much the child has eaten; interact with the child - During illness breastfeed more frequently, provide fluids - After illness give more food at each sitting and feed more frequently until the child has regained weight - Vitamin A at 18 months - Give iron supplements beginning 12 months {GOI policy, available for about 50% of children} |

(Note: The key difference between the control (ICDS) and intervention arms is one of execution and coordination)

## Research Objectives

The main objective of the evaluation is to determine the effectiveness of the “basic” package of INHP-II interventions in terms of reducing child undernutrition of the child in the first 24 months of life. The effectiveness of this ‘basic’ package is to be compared to that of the ICDS package.

A second objective is to make a preliminary assessment of whether the INHP-II strategy is more suited by design to reducing 0 to 24 months child undernutrition only in ecological settings with relatively low economic and cultural constraints to reducing malnutrition. To arrive at an understanding of this, the proposed ER will examine differential impact of INHP-II in a relatively low-constraint ecological setting in India, AP, and a relatively high-constraint setting, UP.

## Proposed Evaluation Research Design

To address the objectives of the evaluation, three evaluation components are proposed (see Figure 1).

1. A pre-test, post-test of control versus program areas (or quasi-experimental design) will be used to assess the effectiveness of the intervention package in improving the nutritional status of children 0-24 months of age. The outcomes of interest are child anemia and underweight. As shown in Figure 1, cross-sectional surveys will be conducted among mothers and children 0-24 months of age in each arm in each site.
2. A collection of methodologies will be implemented to evaluate the process of implementation of the intervention in each site in terms of coverage, dose and fidelity.
3. A longitudinal design will be employed in UP to follow a cohort of women from late pregnancy and their children through (at least) 18 months of age to further examine program effectiveness as well as the specific programmatic experiences as they evolve over time.

***Relative Roles/ Collaborative Partners***

The INHP-II package will be implemented by CARE India. The evaluation methodology has been designed by Johns Hopkins University (JHU). The evaluation will be implemented by Johns Hopkins University (JHU) in partnership with CARE India and King Georges Medical University (KGMU) in Lucknow, India. The evaluation is expected to be conducted through contracts with survey research firms in UP and AP. JHU will conduct and support the analysis of data in both AP and UP.

**Figure 1. CARE India Evaluation Framework for INHP**

**Baseline Survey***

Cross-sectional

2 arms X 2 sites

12/03 – 2/04

3200 respondents per arm

**

**Final Survey***

Cross-sectional

2 arms X 2 sites

2-3/06

3200 respondents per arm

**Program Implementation**

**2/2004-1/2006 (24 months)**

**Process Evaluation**

Semi-annual adequacy surveys and report abstraction

***Survey measures**

Maternal/child anthropometry

Maternal/child morbidity

Maternal dietary pattern

Maternal hemoglobin status

Child feeding pattern

SES

Health care utilization

Adherence

Exposure to program elements

****Cohort measures**

Maternal/child anthropometry

Maternal/child morbidity

Child feeding pattern

Child dietary intakes

SES

Health care utilization

Adherence

Exposure to program elements

Contacts, advices

Immunization

## Sampling Frame

The sampling strategy for the evaluation is as follows. In both AP and UP, an INHP district will be selected as an intervention area while a similar non-INHP (ICDS) district will serve as comparison, giving a total of two districts sampled per state. In UP, Barabanki has been selected as the intervention district and Unnao as the control district. In AP, Karimnagar has been selected as the intervention district and Rangareddy as the control district.

The implementation approach of INHP is that of demonstrating the effect of a technical interventions package delivered through a set of best practices that are designed to maximize effectiveness in improving nutrition and health of children, and the subsequent systematic replication of these best practices.

Approximately 10% of the *Anganwadi* centers[[1]](#footnote-2) (AWCs) “covered” by INHP are demonstration sites. A demonstration site is characterised as an AWC which holds a Nutrition and Health Day, has a Community Based Organization (CBO) which is engaged in nutrition and health activities, has active change agents, has other need-based innovations which serve as the learning ground for the project. Replication is undertaken through focused and deliberate capacity building of government counterparts and systems strengthening in the remaining 90 % areas.

INHP has so far demonstrated four best practices, which have been found to be effective for service delivery and bringing about behaviour change. These are:

- Block Level resource mapping (BLRM)[[2]](#footnote-3)
- Nutrition and Health Days (NHDs)[[3]](#footnote-4)
- Change agents (CAs)[[4]](#footnote-5)
- Community Based Monitoring System (CBMS)[[5]](#footnote-6)

In this context INHP has laid out the year-wise milestones for replication. Therefore, while conducting the evaluation research, it is crucial to identify areas (blocks, sectors and AWCs) that will receive the project interventions through the replication mode. These areas identified for possible replication should then serve as a universe for sample selection, contrary to the entire district serving as a universe for sample selection.

In an intervention district, following steps will be followed to establish the universe for sample selection:

- As a first step, blocks will be identified where the respective ICDS block officials {Child Development Project Officer (CDPO)} are willing to undertake replication. It is likely that out of 10-14 blocks in the district, about 4-5 blocks are selected.
- Subsequently the respective CDPOs will identify next level of functionaries named as sector supervisors that can undertake replication in their areas. A block generally comprises of 3 to 5 sectors and therefore 2 to 3 sector supervisor's areas will be further identified for possible replication.
- As each sector comprises of 20 to 25 AWCs, the respective sector supervisors will then identify *Angawadi* Workers (AWWs) that can undertake replication activities within their AWCs area. It is expected that each identified sector supervisor will have at least 10 to 15 AWWs and their respective AWCs identified as replication sites.
- Therefore, in a district, it is likely that about 150 to 250 AWCs will be identified for replication for the first phase of replication. These selected AWCs can then serve as a universe for sample selection for establishing the baseline for the nutrition evaluation research.
- The AWCs selected through this procedure will be those that receive project intervention for the maximum duration of time as they will be the first to be identified as replication sites.

On the other hand, in the control district, any four blocks can be randomly selected and one sector per block will be randomly selected to get the desired number of AWCs.

***Sampling Design***

**Component 1: Cross-sectional evaluation surveys**

As shown in figure 1, a survey will be conducted during January 2004 - February 2004 for the purposes of providing baseline information on the comparability of the study arms in each of the two study sites. A second survey is planned during January-March 2006 to assess and compare key program indicators and nutritional outcomes across sites. The post-test survey will be conducted at the beginning of 2006, allowing about 24 months for the intervention period before the evaluation, and 12 months afterward for data analysis and dissemination of results. No mid-term evaluation is planned due to cost considerations; rather we intend to rely on information gathered from the cohort study and the process evaluation. A survey research firm will be identified to conduct these surveys in each site, as is being done in the Neonatal Care ER.

**Sample size for baseline and endline surveys**

Sample size is calculated to detect differences in various nutrition outcomes between each intervention district and its comparison district. Assumptions in making these calculations included a statistical power of 80% to detect a difference and a significance level of 95% (alpha = 0.05). The sample size is not increased to account for a design effect, which in nutrition studies has been small or trivial. The sample size estimations for children is based on three primary outcomes: shift in average z-scores in length and weight, stunting and anemia. Calculations for the primary outcomes for children and pregnant women are found in below.

**Table 2.1. Target sample size calculations for primary nutritional outcomes in cross-sectional surveys at baseline and 24 months**

| Outcome Measure | SD or P0 | Detectable difference in means by intervention arm | Sample size  per intervention arm* |
| --- | --- | --- | --- |
| Nutritional status  Children  Shift in average z-score  12-17 months  18-23 months  Stunting (%)  12-23 months | 1.1  1.1  60% | .18 z-score  .18 z-score  Absolute reduction 6% | 587 ~600  587 ~600  1101 ~1200 |
| Anemia  Children 12-23 months    Pregnant women | 80%  50% | Absolute reduction 6%  Absolute reduction 8% | 772 ~800  633 ~800 |

*Estimated sample size rounded to nearest ‘00.

We need approximately 1200 children aged 12-23 months for nutritional status outcomes and at least 800 children for anemia. The NFHS-2 data show that the prevalence of stunting (height-for-age <-2 SD of median of reference population) among children 12-23 months was 57.5%. We estimated a minimum sample size requirement of 1101 children for the detection of 6% absolute reduction in stunting from a 60% prevalence of stunting at baseline. We rounded the target sample to 1200 children aged 12-23 months. The target 1200 sample size is also sufficient to detect a change of at least 0.18 z-score units for anthropometric z-scores.

NFHS-2 reports that the prevalence of anemia among children aged 12-23 months nationally was 77.7% (children aged <3 years: 74.3% nationally, 73.9% in Uttar Pradesh, and 72.3% in Andhra Pradesh). We estimate that a sample of 772 children could detect a 6% reduction in anemia from the assumed 80% prevalence at baseline among children aged 12-23 months. However, recruitment for hemoglobin assessment includes all children 12-23 months of age who will be enrolled in the surveys for anthropometry and an interview, yielding a larger sample. For women of reproductive age, the prevalence of anemia was 51.8% nationally (48.7% in Uttar Pradesh and 49.8% in Andhra Pradesh). We estimate a minimum sample size requirement of 633 (~800) pregnant women to detect a 8% reduction in anemia prevalence.

Sample size for adequacy surveys

For the 2 adequacy surveys, we target 100 currently pregnant women and 500 mothers of children 0-23 months of age for interviews. The purpose of the adequacy surveys is to monitor the progress and implementation of the INHP-II intervention for various process indicators (e.g., home visits received, antenatal iron-folic acid supplements received), and statistical power is not a primary consideration in sample size estimation. However, we estimate the required sample size of at least 97 currently pregnant women to estimate the process indicators with 10% margin-of-error, and round the sample size to 100 pregnant women for the adequacy surveys. With a target sample of 500 mothers of children 0-23 months, we expect to detect at least a 9% difference in program coverage between the arms.

Based on population size, we need 24 and 13 AWC areas in AP and UP districts, respectively, to meet the sample size requirements.

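### Table 2.1 sizes the surveys for one two-group comparison, but the pre-test/post-test design calls for a difference in change, for which power on stunting is about 56%

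*Protocol*

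**What the plan says.** The section on the proposed evaluation design states: "A pre-test, post-test of control versus program areas (or quasi-experimental design) will be used to assess the effectiveness of the intervention package". Figure 1 shows separate cross-sectional surveys at baseline and endline, with two arms in each of two states. The Sampling Frame section pairs one chosen INHP district with one similar non-INHP district per state.

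The section on sample size for the baseline and endline surveys gives the contrast as follows: "Sample size is calculated to detect differences in various nutrition outcomes between each intervention district and its comparison district". It assumes "a statistical power of 80% to detect a difference" and "a significance level of 95% (alpha = 0.05"). On stunting it says: "We estimated a minimum sample size requirement of 1101 children for the detection of 6% absolute reduction in stunting from a 60% prevalence". The target follows: "We rounded the target sample to 1200 children aged 12-23 months". That target is also called "sufficient to detect a change of at least 0.18 z-score units for anthropometric z-scores". On child anemia: "We estimate that a sample of 772 children could detect a 6% reduction in anemia from the assumed 80% prevalence at baseline". Table 2.1 adds 587 (about 600) children for each six-month age band and 633 (about 800) pregnant women. No design effect is applied.

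Component 1 gives the purpose of the baseline survey as showing whether the arms are comparable. It gives the purpose of the second survey as assessing and comparing indicators and outcomes.

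**The concern.** These sections do not describe the same contrast. A controlled pre-test/post-test design in non-randomised districts estimates the program effect as the change in the program district minus the change in its control. That estimate carries the sampling error of four surveys, about twice the variance of a single comparison between two districts. Table 2.1 allows for two samples only.

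The baseline matters here because the areas were not selected alike. Under Sampling Frame, intervention sites come from officials, supervisors and workers willing or able to replicate the program. Under Sample Selection, four Barabanki blocks with too many supervisor vacancies are left out, while control blocks are drawn at random. Differences that exist before the program are therefore plausible, and an endline-only comparison would attribute them to it.

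If the result is analysed as a difference in change, a null finding on stunting could be read as evidence from a study with 80% power, although a true 6-point effect would be missed about 44% of the time.

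**Working it through.** **Inputs (Table 2.1 and accompanying text).** Stunting 60% to 54%; child anemia 80% to 74%; anemia in pregnant women 50% to 42%; z-score SD 1.1 and difference 0.18; alpha 0.05; power 80%. Sidedness is not stated, but only two-sided calculations reproduce the table.

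**Step 1: reproduce the plan's figures as single two-group comparisons.**

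- z-score: n = 2 × [1.1 × (1.960 + 0.842) / 0.18]² = 587.
- Proportions: n = [1.960 × √(2p̄(1 − p̄)) + 0.842 × √(p₀(1 − p₀) + p₁(1 − p₁))]² / (p₀ − p₁)², where p̄ is the mean of p₀ and p₁.
  - Stunting: 1,068, or 1,101 with continuity correction.
  - Child anemia: 772 without continuity correction (805 with it).
  - Pregnant women: 609, or 633 with continuity correction.

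All four published figures (587, 1,101, 772, 633) are matched. The uneven use of the continuity correction is minor.

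**Step 2: power for the difference in change.** Take four independent samples of n each (two districts, two rounds), with control prevalence constant at p₀ and no design effect.

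- Proportions: SE = √{[3p₀(1 − p₀) + p₁(1 − p₁)] / n}
- Means: SE = 1.1 × √(4/n)
- Power = Φ(effect/SE − 1.960)
- Detectable difference at 80% power = 2.802 × SE

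Stunting at 1,200: SE = √[(3 × 0.24 + 0.2484)/1,200] = 0.0284. Then 0.06/0.0284 = 2.112, and Φ(0.152) = 56.0%. The detectable difference is 2.802 × 0.0284 = 8.0 points.

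| Outcome and effect | n per cell | Power | Detectable at 80% |
| --- | --- | --- | --- |
| Stunting, 6 points | 1,200 | 56.0% | 8.0 points |
| z-score 0.18, one age band | 600 | 51.8% | 0.25 |
| z-score 0.18, pooled 12-23 months | 1,200 | 80.9% | 0.178 |
| Child anemia, 6 points | 800 | 54.4% | 8.1 points |
| Child anemia, 6 points | 1,200 | 71.7% | 6.6 points |
| Pregnant women, 8 points | 800 | 62.2% | 9.9 points |

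The second child anemia row applies because the protocol says hemoglobin is measured in all surveyed children of 12-23 months, not only 800.

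**Step 3: sample size that would keep the stated effects at 80% power.** Solving for n gives, per cell, 2,112 for stunting, 1,466 for child anemia, 1,219 for pregnant women and 1,173 for the z-score (per band if the bands stay separate).

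**Step 4: sensitivity.** If stunting fell by 3 points in both districts for other reasons, power would still be about 56%. An assumed design effect of 1.2 would take it to about 49%: 0.06/(0.0284 × √1.2) − 1.960 = −0.03.

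**Step 5: what the endline-only contrast risks.** As an illustration, assume a pre-existing 3-point stunting gap (60% versus 57%) and no program effect. SE = √[(0.24 + 0.2451)/1,200] = 0.0201, and 0.03/0.0201 = 1.49. The comparison would be significant about 32% of the time.

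**The case against.** The strongest defence is that the table is right for the contrast it names. All four figures reproduce, and 80% is correct for a district-versus-district comparison; for stunting at 1,200 it is about 84%. The protocol nowhere names a difference-in-differences estimator. Its account of the baseline as a comparability check fits an endline comparison, and the sociodemographic questionnaire would supply covariates for adjustment. The analysis plan, which is not at hand, may settle the estimator.

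Much of this stands. A reader might infer that the sample sizes were miscalculated; they were not. A reader might infer that the protocol commits itself to a difference in change and so has 52-56% power across the board. It makes no such commitment, and that range does not cover child anemia at about 1,200, pregnant women at 800 or the pooled z-score. The sentence saying that 1,200 children suffice for 0.18 z is correct even for the difference in change, before any design effect.

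What does not stand is leaving the matter there. The design statement, the power claim and effects worded as reductions from a baseline prevalence are all in the protocol, and they point to different contrasts. An endline-only analysis would save the 80% but would not use the pre-test/post-test design, and a comparability check does not remove a gap that it finds. Covariate adjustment, or returning to the same AWC areas, might recover some precision. Table 2.1 claims no such gain, however, and the protocol repeats the selection process at endline without saying that the same areas are kept.

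**Conclusion.** The point holds as a mismatch between design and sample size, not as an arithmetic error. The stated 80% power belongs to an endline-only contrast. For the contrast that the pre-test/post-test design needs, the outcome that sets the 1,200 target (stunting) has about 56% power for 6 points and can detect 8.0 points with 80% power. The other outcomes range from 52% (z-score by age band) to 81% (z-score pooled over 12-23 months).

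These figures assume independent surveys, equal cells, constant control prevalence, a two-sided 5% test and no design effect. A design effect above 1 would lower them; covariate adjustment could raise them.

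**What to change.** Name the within-state arm-by-round difference in change as the primary contrast, and bring the description of the baseline survey's purpose into line with it. Restate Table 2.1's 80%-power detectable differences for that contrast, marked as before any design effect:

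- stunting: 8.0 points at 1,200;
- child anemia: 6.6 points at 1,200;
- anemia in pregnant women: 9.9 points at 800;
- z-scores: 0.25 per 600-child band, or 0.178 pooled at 1,200.

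Optionally, make the pooled, age-adjusted 12-23-month z-score analysis primary and keep the two age bands as secondary. This recovers the stated 0.18 with the children already planned, but gives up separately powered claims for each band.

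The cost is wording and a corrected table, with no extra enrolment. The trade-off is an open statement that the surveys are less sensitive than now claimed; keeping 6 points of stunting at 80% power would instead take about 2,112 children per cell.

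### The AP-versus-UP objective has no matching contrast, and the stated 80% power holds only for an endline-only comparison, not for the pre/post design

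*Protocol*

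**What the plan says.** Under Research Objectives, the Protocol first asks how effective the basic package is compared with ICDS. It then sets a second objective, described as a preliminary assessment, for which the evaluation "will examine differential impact of INHP-II in a relatively low-constraint ecological setting in India, AP, and a relatively high-constraint setting, UP".

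Proposed Evaluation Research Design (item 1) names a before-and-after comparison of programme and control areas as the design for effectiveness, with cross-sectional surveys in each arm and site.

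The section Sample size for baseline and endline surveys states: "Sample size is calculated to detect differences in various nutrition outcomes between each intervention district and its comparison district". It uses 80% power, alpha 0.05 and no design effect. For stunting it gives a "minimum sample size requirement of 1101 children for the detection of 6% absolute reduction in stunting from a 60% prevalence of stunting at baseline", and adds: "We rounded the target sample to 1200 children aged 12-23 months". The same 1,200 is called "sufficient to detect a change of at least 0.18 z-score units for anthropometric z-scores".

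Under Component 1, the endline survey is meant "to assess and compare key program indicators and nutritional outcomes across sites". The Background says that AP "has better nutritional status compared to all India figures" and that UP has high rates of child undernutrition.

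**The concern.** A difference in impact between two states is a contrast of two effects. With baseline and endline surveys it is the AP arm-by-round effect minus the UP arm-by-round effect. The sample-size section covers neither this contrast nor its precision. The Protocol does describe a cross-state comparison of endline outcomes. In the design section, in Figure 1 and in the sentence just before the endline one, *site* denotes a state. On that reading the comparison is of endline levels in AP and UP, and AP's head start would enter what looks like an effect.

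There is a related mismatch in the power statement. Subtracting the baseline difference adds the sampling error of two more surveys, so a size that gives 80% for endline alone gives less for pre/post.

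At stake is how the second objective will be read. The states carry low- and high-constraint labels in advance, so a significant result in AP only could be taken as an answer although it is not a test of a difference.

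**Working it through.** **Inputs.** All come from Table 2.1 and the text around it: stunting 60% to 54%, 1,200 per district per survey; z-scores SD 1.1, difference 0.18, 600 per six-month age band or 1,200 over 12-23 months; child anemia 80% to 74%, 1,200, because all enrolled children aged 12-23 months are to be tested; anemia in pregnant women 50% to 42%, 800. Sidedness is not stated; two-sided tests reproduce the figures.

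**1. The Protocol's own figures.**
- Stunting: [1.96√(2 × 0.57 × 0.43) + 0.8416√(0.24 + 0.2484)]² / 0.06² = 1,068, and 1,101 with the continuity correction.
- z-score: 2 × (1.96 + 0.8416)² × 1.1² / 0.18² = 587.
- Child anemia: 772 (no continuity correction).
- Pregnant women: 609, and 633 with the correction.

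All four are reproduced as two-group comparisons at one time point. At 1,200 per arm, the endline stunting contrast has 84% power.

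**2. The pre/post contrast within one state.** Assume independent samples, both districts at the baseline rate p₀ in the first survey, the control district still at p₀ at endline, and the intervention district at p₁. Then variance = [3p₀(1−p₀) + p₁(1−p₁)]/n and power = Φ(difference/SE − 1.96).

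Stunting: (0.72 + 0.2484)/1,200 = 0.000807, so SE = 2.84 points, 6/2.84 = 2.11 and power = 56%. For z-scores, SE = 1.1√(4/n). An equal-weight average over two states halves the variance.

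| Outcome (n per district per survey) | Pre/post, per state | Pre/post, averaged over states |
|---|---|---|
| Stunting (1,200) | 56% | 85% |
| z-score, one age band (600) | 52% | 81% |
| z-score, 12-23 months (1,200) | 81% | 98% |
| Child anemia (1,200) | 72% | 95% |
| Pregnant women, anemia (800) | 62% | 89% |

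**3. The AP-minus-UP difference in stunting effect.** Take 6 points in one state and none in the other, 1,200 per district.
- Endline only: SE = √[(0.24 × 3 + 0.2484)/1,200] = 2.84 points; power 56%.
- Pre/post: SE = √[(0.24 × 7 + 0.2484)/1,200] = 4.01 points; power 32%.
- Difference detectable with 80% power, using 54% in both intervention districts for the variance: 2.80 × √[2 × 0.4884/1,200] = 8.0 points endline only; 2.80 × √[2 × 0.9684/1,200] = 11.3 points pre/post.

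**4. A chance split between states.** If true effects are equal and each state is judged by its own test with power p, significance in AP but not UP has probability p(1−p). For stunting this is 0.844 × 0.156 = 13% (endline) and 0.560 × 0.440 = 25% (pre/post). A split in either direction is twice as likely. At endline and target size it is lower for other outcomes: 9% for pregnant women, 6% for child anemia, 2% for z-scores at 1,200.

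**5. Sensitivity.** The Protocol gives no design effect. Assuming 1.5 or 2, pre/post stunting power falls to 41% or 32% per state, and to 68% or 56% averaged.

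**The case against.** A sample-size sentence says how n was chosen, not how effects will be estimated. The Protocol names no model or test, and the estimator is ordinary content for an analysis plan, which is not shown. A reader might infer that the states will be judged by two separate p-values, or that pooling is excluded. Neither is stated, so the 13% to 25% describes a risk to guard against, not a planned procedure.

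A reader might also infer that the main objective is short of power. That fails for the contrast actually sized: each state meets 80% at endline, and sizing each state alone is the conservative choice. The baseline survey is also described as informing arm comparability, which leaves an endline-only analysis possible. Nor does the Protocol say that the first objective is one averaged effect. It chose two distinct states deliberately, so state-specific effects are a legitimate target and making the average primary would be partly preference.

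The across-sites phrase could mean comparing arms in both states. And the second objective is preliminary, so the absence of formal power for it is not in itself an error.

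These points limit the finding but do not remove it. Objectives and the basis for sample size are protocol content. A preliminary objective still needs a contrast that answers it, and the literal endline comparison does not. The design section calls the evaluation pre/post, so power for that contrast should be given.

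**Conclusion.** The point holds in two parts. First, the AP-versus-UP objective has no stated contrast that measures a difference in impact. The design could detect about 11 points in stunting with 80% power pre/post (about 8 endline only), against a planned effect of 6 points. Second, the stated 80% applies to an endline-only arm contrast. On the named pre/post design, power per state runs from 52% (z-score in one age band) to 81% (z-score over 12-23 months), with stunting at 56%.

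The documents do not support saying that neither objective can be estimated, or that a false AP-only result is built into the plan.

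The figures assume the Protocol's rates, equal baselines in the paired districts, two-sided tests and no design effect. They are upper bounds: clustering is ignored, and with one district per arm per state, variation between districts cannot be estimated.

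**What to change.** - **Component 1, endline sentence:** say that the second objective is assessed by the AP-minus-UP difference in the arm-by-round effect, with a 95% confidence interval. Say that it is not judged from endline levels across states or from two state p-values. State the detectable difference in stunting: about 11 points, or about 8 if endline only.
- **Sample-size section:** restate power per state for the pre/post contrast, and say that no design effect is included. Add a state-stratified average arm-by-round effect for the first objective (about 85% power for stunting) beside the state-specific estimates.

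The cost is wording and one additional model per outcome; no new data are needed. The average can hide heterogeneity between the states, which the state estimates and the AP-minus-UP difference would then show.
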